1. INTRODUCTION: BACKGROUND INFORMATION AND SCIENTIFIC RATIONALE
   1. Background Information

Dengue is a mosquito borne flavivirus infection that occurs in the tropical and sub-tropical regions of the world. World Health Organization (WHO) lists dengue among one of the seventeen prioritized, neglected tropical diseases that affects more than a billion populations. According to its most recent epidemiological data, dengue has a yearly incidence of about 50-100 million cases, with 40% of the global population considered at risk for dengue^1^. As the vector habitat expands, dengue outbreaks have become a common occurrence in Asia, especially India. Recent data from WHO reports the case fatality rate of dengue at 2.5% and the estimated morbidity and mortality due to dengue infection as approximately 1,300 disability-adjusted life years (DALYs) per million^2^. These figures clearly highlight the severe impact dengue infection can have on the public healthcare costs and resources. In India, dengue is endemic or hyperendemic in most parts and the healthcare and economic cost of regular and isolated outbreaks can be very high as estimated in the recent study by *Shepard et al*^3^.

Dengue is known to be heterogeneous in its clinical presentation and the unpredictable nature of its severity and outcomes often proves to be a challenge to the clinician. While a majority of dengue infections resolve rapidly after presenting as mild asymptomatic febrile illness, a small percentage of dengue infected cases progress to severe disease characterized by excessive bleeding and plasma leakage that can eventually lead to shock (DSS) and death. Management of dengue is largely based on providing timely, appropriate and supportive treatment. In order to facilitate early diagnosis and timely management of severe dengue, the WHO in 2009 introduced a new set of criteria for its clinical classification based on its severity. Based on clinical severity criteria, dengue cases are now categorized as ‘dengue with’ or ‘dengue without’ warning signs and severe dengue^5^.

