1. OBJECTIVES
   1. Study Objectives

Thrombocytopenia is a well-known risk factor of fatality in severe dengue cases. A steady decline in platelet counts is characteristically associated with dengue illness severity. Thrombocytopenia coupled to severe vascular leakage and shock, usually around the time of defervescence can prove to be fatal. We hypothesize that administration of CPLE (Caripill) tab early in the course of dengue illness increase the platelet counts and reduce the likelihood of severe complications.

The clinical benefit of CPLE (Caripill) administration on the platelet counts in mild and moderate dengue have been shown before, this study will present an opportunity to specifically evaluate the effectiveness of CPLE (Caripill) administration in severe thrombocytopenic (≤ 30,000/µL) dengue cases. We will also investigate the effect of CPLE on the viremia (or NS1 antigenemia) as well as the infection induced immune response.

Primary Objectives:

1. To evaluate if CPLE (Caripill) administration (1100 mg three times a day for 5 days) in dengue patients with thrombocytopenia ≤30,000/µL is superior to placebo with respect to improvement in platelet counts and hematocrit values.
2. To evaluate if CPLE (Caripill) administration (1100mg three times a day for 5 days) in dengue patients with thrombocytopenia ≤30,000/µL is superior to placebo with respect in reducing the number of platelet transfusions needed in management.
3. To determine and compare the incidence of bleeding episodes during hospitalization between the treatment and placebo groups. Bleeding will be defined as mucosal bleeds such as subcutaneous bleeding, minor mucosal hemorrhages, sub-conjunctival hemorrhage, epistaxis, petechiae, or ecchymosis, positive tourniquet test.
4. To evaluate the final outcome of dengue illness (survival/mortality rates) between the treatment and placebo groups.

Secondary Objectives:

1. To correlate the changes in platelet counts to the clinical phase of dengue illness (febrile/critical (plasma leak)/ convalescent) between the treatment and placebo groups.
2. To compare and evaluate the viremia (or NS1 antigenemia) with peripheral platelet counts between the treatment and placebo groups.
3. To evaluate length of hospital (ICU & ward) stay in patients receiving CPLE (Caripill) for severe dengue.
4. To compare and evaluate the levels cytokines TNFα, IFNγ, IL4 and IL6, on day 0, and 3 of study period between the treatment and placebo groups.

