   1. Study Outcome Measures
      1. Primary

The primary efficacy endpoints will be assessed by comparing the increase in the platelet counts and hematocrit levels during the hospital stay between the treatment and placebo groups. The peak platelet count and hematocrit will also be noted and compared between the treatment and the placebo group. Additionally, the frequency and type of blood product, more specifically platelet transfusions required to manage thrombocytopenia during the course of illness will be compared between the two study arms.

Safety and tolerability will also be evaluated by comparing the proportion of patients with any AE (adverse event), and with any SAEs, between the treatment arms. The incidence of bleeding episodes as assessed by clinical evaluation twice daily between the treatment and placebo groups will also be evaluated. Evidences of subcutaneous bleeding minor mucosal hemorrhages, sub-conjunctival hemorrhage, epistaxis, petechiae, or ecchymosis), positive tourniquet test, hypotension and internal organ bleeding, hematemesis, intracranial bleed and melena will be assessed.

- - 1. Secondary

Secondary outcomes that we plan to evaluate include parameters indicative of disease progression or worsening of illness. These will be compared between the two study arms.

1. To correlate the change in platelet counts and subsequent response with or without CPLE (Caripill) to the phase of dengue (febrile/critical (plasma leak)/ convalescent) We will study the correlation of the duration of moderate to severe thrombocytopenia with the phase of the dengue- febrile, critical-plasma leak, convalescence. Additionally we will compare both arms of the study to examine if the intervention in any of the three phases affected the duration/severity of thrombocytopenia.
2. The type of bleeding manifestation between the two arms of the study will be characterized. We will examine the evidence of (mucosal, GI, GU, vaginal, IC bleed etc.) bleeding with severity of thrombocytopenia and response to intervention by comparing both arms.
3. Date of admission and date of discharge or death will be noted in the CRFs and will be used to determine the length of hospital stay (ICU & Ward), in severe thrombocytopenic dengue patients receiving CPLE (Caripill) treatment compared to the placebo group.

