**5.1 Subject Inclusion Criteria**

In order to be eligible to participate in this study, an individual must meet all of the following criteria:

1. Provide signed and dated informed consent form
2. Willing to comply with all study procedures and be available for the duration of the study
3. Male or female, aged ≥ 18 yrs of age. Clinically diagnosed of dengue and a peripheral platelet count of ≤30,000/µL.
4. A laboratory positive diagnosis of dengue confirmed by a positive NS1 or IgM or IgG ELISA test and/or detection of viral RNA by real time PCR assay.

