1. STUDY SCHEDULE

Screening

All adult patients admitted to Gen Medicine with a history of fever (<72 hr) will be clinically and laboratory evaluated for dengue illness. Subsequent to obtaining and documenting an informed consent form, the study subject will be further screened for detailed laboratory diagnosis for dengue and reviewed clinically for satisfying all study inclusion and exclusion criteria. Details in Schedule of Events

Detailed history and clinical examination will be performed and data recorded in the study CRF. Baseline hematological and biochemical, virological parameters (as part of standard of care) will be sought and recorded in the CRF. Study subject will be administered the study medications on day 1 after confirmed diagnosis as per schedule. Clinical evaluations, laboratory investigations including viral load will be performed during hospital stay.

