**10.3: Sub-group Analyses:**

Pre-defined secondary endpoints will be compared between the two treatment arms based on linear regression for continuous endpoints, logistic regression for binary endpoints, and Cox regression for time-to-event endpoints. For laboratory markers, comparisons will be adjusted for the pre-dose value of the respective marker and the day of illness at enrolment; plasma cytokines and NS1-endpoints will additionally be adjusted for dengue illness phase.

A detailed statistical analysis plan will be finalized prior to unblinding the study data base.

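### Length of stay ends at discharge or death alike, so an early death counts as a short stay; the bias is small, and a definition based on discharge alive removes it

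*Protocol*

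**What the plan says.** The secondary objectives in the Protocol include: "To evaluate length of hospital (ICU & ward) stay in patients receiving CPLE (Caripill) for severe dengue". Item 3 of the secondary outcome measures gives the definition: "Date of admission and date of discharge or death will be noted in the CRFs and will be used to determine the length" of stay, for comparison with placebo. The interval therefore has one start, admission, and one end that discharge and death share.

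Mortality is a separate primary objective: "To evaluate the final outcome of dengue illness (survival/mortality rates) between the treatment and placebo groups".

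Section 10.3 analyses secondary endpoints by linear regression if continuous, logistic regression if binary, and "Cox regression for time-to-event endpoints". It does not say which of these applies to length of stay. Section 10.2 has a censoring rule for loss to follow-up and none for death. Section 10.3 defers further detail to an analysis plan to be finalised before unblinding.

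**The concern.** The Protocol introduces its secondary outcomes as markers of progression or worsening, so a shorter stay would be read as benefit. Under item 3 the worst course of illness, early death, gives one of the shortest stays. If one arm has more early deaths, its mean or median stay falls, and its rate of reaching the end of stay rises, for a reason that is the opposite of benefit.

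The available models do not repair this:

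- **Linear regression** on days uses the short value as it stands.
- **Cox regression** with item 3's end date counts death as the same event as discharge.
- **Cox regression censored at the date of death** is not right either. It treats the dead patient as someone who would have gone on to be discharged at the same rate as those still in hospital.

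What is at stake is a claim of shorter stay to which deaths have contributed.

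**Working it through.** The Protocol gives no effect size, standard deviation or power for length of stay, so there is no stated figure to reproduce. The check asks how far item 3's definition can move the comparison.

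**Inputs from the Protocol**

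- 50 patients per arm (study schematic).
- A "case fatality rate of dengue at 2.5" per cent (Introduction). This is for dengue in general; no rate is given for patients at or below the platelet entry threshold.

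**Assumed inputs**

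- A death shortens the stay by 4 days, with 5 days as an alternative. This corresponds to survivors staying 7 days and deaths occurring at day 3 or day 2.
- The standard deviation of stay is 2 days.

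**Expected deaths.** 100 × 0.025 = 2.5 in the trial, or 1.25 per arm. The chance of at least one death is 1 − 0.975^100 = 0.92. The rule will probably be needed, but for very few patients.

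**Shift in mean stay.** If survivors stay L days on average, deaths occur after D days, and the death rate is p, an arm's mean stay is (1 − p)L + pD = L − p(L − D). With L and D the same in both arms, the spurious difference between arms is (p1 − p2)(L − D), in favour of the arm with more deaths.

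| Death rates | Difference | Shift if L − D = 4 days | Shift if L − D = 5 days |
|---|---|---|---|
| equal in both arms | 0 | 0 | 0 |
| one extra death in 50 | 0.02 | 0.08 day | 0.10 day |
| 5% v 2.5% | 0.025 | 0.10 day | 0.125 day |
| 10% v 5% | 0.05 | 0.20 day | 0.25 day |
| 8% v 2% | 0.06 | 0.24 day | 0.30 day |

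**Against sampling error.** With the assumed SD, the standard error of the difference is 2 × √(2/50) = 0.40 day. One extra death is 0.08/0.40 = 0.2 standard errors. The 8% v 2% row at 4 days is 0.24/0.40 = 0.6 standard errors.

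**Direction.** The sign holds for deaths that come before the usual day of discharge (D < L). A death after a long ICU stay would push the mean the other way. A definition based on discharge alive handles both cases.

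**The case against.** The best defence is that item 3 names dates and leaves the analysis open: length of stay is assigned to no model, and an analysis plan is promised. That is partly right, because the choice of model is still free. But the start and the shared end of the interval are fixed in the Protocol, and a plan that follows the text inherits them.

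It is also fair to say that the effect is small and that mortality is compared on its own, so a marked imbalance in deaths would be seen beside the length-of-stay result. Both points stand. They limit the importance of the finding but do not make the definition right.

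A reader might infer more from the start date. Screening takes place after admission: "All adult patients admitted to Gen Medicine with a history of fever (<72 hr) will be clinically and laboratory evaluated for dengue illness". Dosing follows later: "Study subject will be administered the study medications on day 1 after confirmed diagnosis as per schedule". Days before randomisation cannot respond to treatment, so it is tempting to call the comparison biased or short of power. The documents do not support either claim:

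- Randomisation balances those days in expectation, so they cause no bias.
- Counting from admission matches the objective in the Protocol Summary, which is total hospital stay.
- A loss of power cannot be quantified. The Protocol gives no spread for the days before or after randomisation, and the two may be negatively correlated, since the Background ties platelet fall and recovery to the course of the fever. With assumed SDs of 2 days after and 1 day before, a correlation of −0.25 gives a total variance of 4 + 1 − 2 × 0.25 × 2 × 1 = 4, which is no loss at all.

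**Conclusion.** The definition in item 3 is faulty in one respect: it lets an early death count as a short stay, and nothing else in the Protocol prevents this. The bias favours the arm with more early deaths. Its likely size is about 0.08 day for a one-death imbalance at 50 per arm, given the assumed 4-day cut. At equal death rates its expected value is zero. It becomes larger only if mortality in these patients exceeds the cited figure and differs between arms; the higher rows of the table are illustrations, and no rate in the documents supports them.

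The start at admission is not an error. Counting from randomisation would be a choice made for precision.

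Severity is minor: one secondary endpoint, in a trial that section 10.1 calls exploratory.

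**What to change.** 1. In item 3 or the analysis plan, before unblinding, define the event as discharge alive and state that death is never counted as discharge. Either analyse death as a competing event, or keep patients who die in the Cox model of section 10.3 as not discharged and censor them at the end of the 2-week follow-up. State that end as one study day, because Study Design places the visit at week 2 and the Protocol Summary places it two weeks after the last dose.
2. If mean or median days are reported, rank deaths worst, or also show survivors separately. The survivor figures are descriptive, since survival is itself an outcome.
3. Optionally, analyse days from randomisation and keep total stay from admission as a descriptive figure.

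The first two changes cost a sentence or two of wording. Item 3 already records the date of discharge or death, and the Types of Data section captures mortality, so the two endings can be told apart. A separate analysis of ICU and ward days would need transfer dates. The text does not list these and the case report form is not shown, so their availability should be checked first.

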5. STUDY DESIGN

This study is a randomized, placebo-controlled; double-blind trial investigating CPLE (Caripill) therapy in adult dengue patients with a thrombocytopenia of < 30,000/µL. Adults (≥ 18yrs of age, non-pregnant) and laboratory (+ NS1 ELISA/ + vRNA RTPCR)/+IgM or +IgG) confirmed diagnosis of dengue and with a peripheral platelet count of ≤ 30,000/µL will be enrolled into the study after signing an informed consent form.

The study patients will be followed for clinical and laboratory endpoints in hospital until study day 5 (or daily as out-patients from discharge to day 5) and reviewed at an outpatient visit at week 2.

The patients will be assigned to one of the two treatment arms:

1. Active drug: CPLE (Caripill) CPLE 1100mg *t.i.d* for 5 days.

2) Placebo: visually matched placebo *t.i.d* for 5 days.

Oral tablet of CPLE (Caripill) and placebo will be provided by Micro Labs Ltd with appropriate masking for a double blind study. On receipt the medications will be stored in accordance with the manufacturer’s recommendation in a secure area.

Enrolled patients will be randomly assigned in a 1:1 ratio to receive CPLE (Caripill) or placebo once daily for 5 days. Online randomization software will be used for patient assignment. Only the clinical trials pharmacist will have access to the randomization list.

Micro Labs Ltd will provide CPLE (Caripill) and visually matched placebo without charge. All other study staff will be blinded to treatment allocation until after completion of the study. Each enrolled patient was assigned the next available study code that corresponded to a prepackaged pack of study drug. Clinical data were captured on structured case report forms that were entered into a secure database.

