15 APPENDICES LIST …………………………………………………………………………………………………………..……….33

LIST OF ABBREVIATIONS

| AE | Adverse Event/Adverse Experience |
| --- | --- |
| CONSORT | Consolidated Standards of Reporting Trials |
| CRF | Case Report Form |
| CPLE | *Carica papaya* leaf extract |
| GCP | Good Clinical Practice |
| ICF | Informed Consent Form |
| ICH | International Conference on Harmonization |
| IRB | Institutional Review Board |
| LFT | Liver Function Tests |
| AST | Aspartate Aminotransferase |
| ALT | Alanine Aminotransferase |
| MOP | Manual of Procedures |
| N | Number (typically refers to subjects) |
| PI | Principal Investigator |
| SAE | Serious Adverse Event/Serious Adverse Experience |
| SOP | Standard Operating Procedure |
| UP | Unanticipated Problem |
| WHO | World Health Organization |

PROTOCOL SUMMARY

| **Title:** | A prospective study to evaluate the safety and efficacy of *Carica papaya* leaf extract (oral CPLE (Caripill)) in the treatment of severe thrombocytopenia (≤30,000/µl) in dengue |
| --- | --- |
| **Précis:** | This will be a placebo-controlled, single center, randomized prospective study of CPLE (Caripill) (*Carica papaya* leaf extract) tabs in dengue patients with severe thrombocytopenia (platelets ≤ 30,000/ul). The study will enroll 100 eligible dengue cases into the two arms of the study – one arm receiving CPLE (Caripill) 1100mg *t.i.d* for 5 days and the other group receiving placebo. |
| **Objectives:** | Primary: To determine the impact of CPLE (Caripill) administration (1100mg *t.i.d* for 5 days on the following:   - Platelet count and hematocrit values in dengue patients with severe thrombocytopenia. - Reducing the number of blood product transfusions *esp.* platelet transfusion and - All-cause mortality rates. |
|  | Secondary: To evaluate the effect of CPLE (Caripill) administration (1100mg *t.i.d* for 5 days) on the following-   - Magnitude and kinetics of serum viremia (or NS1 antigenemia). - Magnitude and kinetics of cytokines IFNγ, IL6, TNFα and IL4. - The total length of hospital (ICU & ward) stay, |
| **Population:** | Study cohort of 100 adults, either gender (more than 18 yrs old, non-pregnant) and admitted to AIMS Hospital and diagnosed of dengue with moderate to severe thrombocytopenia. |
| **Number of Sites:** | Dept. of General Medicine and Dept. of Emergency Medicine, Amrita Institute of Medical Sciences and Research Center, [name]. |

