| **Description of Intervention:** | Orally available CPLE (Caripill) Tabs (Micro Labs Ltd) at a dose of 1100 mg/tab three times a day for 5 days |
| **Study Duration:** | The estimated time (in months) from when the study opens to enrollment until completion of data analyses will be 12 months. |
| **Subject Participation Duration:** | Duration of hospital stay and the subsequent follow-up at 2 week post last dose of CPLE (Caripill). |
| **Estimated Time to Complete Enrollment:** | Immediately after screening positive and signing the informed consent form (ICF). |

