**5.4 Treatment Assignment Procedures**

- 1. 1. Randomization Procedures (if applicable)

We will randomly assign enrolled patients in a 1:1 ratio to receive CPLE (Caripill) (1100mg) or placebo once daily for 5 days. Block randomization of will be stratified by age and gender into block sizes of 4 or 6.

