1. STUDY INTERVENTION
   1. Study Product Description

Package Insert information on CPLE (Caripill) tabs

- - 1. Acquisition

CPLE (Caripill) and placebo tablets will be supplied by MicroLabs Ltd.

- - 1. Formulation, Packaging, and Labeling

Packaging and labeling of CPLE (Caripill)

- - 1. Product Storage and Stability

The CPLE (Caripill) tabs will be stored at room temperature, away from heat and direct light.

- 1. Dosage, Preparation and Administration of Study Product

CPLE (Caripill) and placebo tabs of 1100mg in strength will be administered orally three times a day for 5 days.

- 1. Assessment of Subject Compliance with Study Product Administration

Each study subject will be directly observed for patient compliance by pill counts by the study nurse co-ordinator.

- 1. Concomitant Medications/Treatments

The treatment plans including the details of the concomitant medications will be recorded in the case record form (CRFs – Appendix I).

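### Two randomisation sentences give study drug once daily for 5 days, while the arm definitions, summary, schematic, objectives and dosage section give it three times a day

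*Protocol*

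**What the plan says.** Two sentences give a once-daily schedule:

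- Study Design, randomisation sentence: "Enrolled patients will be randomly assigned in a 1:1 ratio to receive CPLE (Caripill) or placebo once daily for 5 days". It gives no milligram amount.
- Section 5.4 (Treatment Assignment Procedures): patients are assigned "to receive CPLE (Caripill) (1100mg) or placebo once daily for 5 days". This is the only place where 1100 mg and once daily appear together.

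The other places that state a frequency give three times a day:

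- Study Design, arm definitions, a few lines above the once-daily sentence: "Active drug: CPLE (Caripill) CPLE 1100mg *t.i.d* for 5 days" and "Placebo: visually matched placebo *t.i.d* for 5 days".
- Protocol Summary, Précis: "one arm receiving CPLE (Caripill) 1100mg *t.i.d* for 5 days and the other group receiving placebo".
- Protocol Summary, Description of Intervention: "at a dose of 1100 mg/tab three times a day for 5 days".
- Schematic of Study Design: three times a day at Day 0 for 5 days, repeated for the following days.
- Objectives, first primary objective: "administration (1100 mg three times a day for 5 days"; the second primary objective states the same schedule.
- Study Intervention, dosage and administration: "CPLE (Caripill) and placebo tabs of 1100mg in strength will be administered orally three times a day for 5 days".

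**The concern.** The dosing frequency is part of the definition of the randomised intervention. The first two primary objectives are framed as superiority of a named regimen over placebo, so the regimen belongs to the question the trial asks. Here the text that assigns patients to treatment disagrees with the text that defines the treatment, and Study Design disagrees with itself.

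The conflict lies in complete sentences of current, operative text. It is not in background material, a damaged table or an amendment log. The once-daily wording occurs in two separate sections, once with its strength, and the protocol has no rule on which section prevails.

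At stake is a clear statement of exposure. Efficacy results, adverse-event proportions and the ALT check 48 hours after enrolment are all read against the amount of product given, and the protocol's sentences put that amount at two different levels. Dosing frequency is protocol content, so a later statistical analysis plan would not be expected to settle it.

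**Working it through.** **Inputs**

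- Strength: 1100 mg per tablet (Protocol Summary, Description of Intervention; Study Intervention, dosage and administration).
- Duration: 5 days in every place.
- Frequency A: once daily (Study Design randomisation sentence; section 5.4).
- Frequency B: three times a day (all other places that state a frequency, including the Study Design arm definitions).
- Tablets per administration: one. This is a reading of the description of 1100 mg per tablet three times a day, and of 1100 mg in section 5.4 as the amount per administration. No sentence states the number of tablets per administration outright.

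**Formulas**

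- Daily dose = strength × administrations per day.
- Tablets per course = administrations per day × days.
- Course total = daily dose × days.

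**Results**

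| | Once daily | Three times a day | Ratio |
|---|---|---|---|
| Daily dose | 1 × 1,100 = 1,100 mg | 3 × 1,100 = 3,300 mg | 3 |
| Tablets per course | 1 × 5 = 5 | 3 × 5 = 15 | 3 |
| Course total | 1,100 × 5 = 5,500 mg | 3,300 × 5 = 16,500 mg | 3 |

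The ratio is 3 after any number of complete treatment days, so it applies to exposure at an early safety check as well as over the full course. The ratio of administrations, 3 to 1, needs no assumption about strength. The milligram and tablet figures rest on one 1100 mg tablet each time.

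**Does it differ by arm?** No. Both once-daily sentences cover CPLE and placebo together. The arm definitions give the same three-times-daily schedule for each arm, and the dosage section covers both kinds of tablet. Whichever version is followed, the two arms have the same number of administrations.

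**Does it reach the sample size?** No. The power statement in section 10.1 refers to a 20% increase in platelet count and hematocrit and uses no dose or frequency.

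**Does anything else in the protocol settle it?** No. The packaging and labelling text gives no tablet number, and the compliance text asks for observation and pill counts without saying how many tablets are expected.

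**The case against.** The strongest reply is that the intended meaning is easy to see: one frequency is stated in many places, including the section devoted to dosing, and the other only in two near-identical randomisation sentences. Administration is to be directly observed with pill counts, so the regimen actually given would be on record. This limits the likely practical harm. It does not remove the contradiction, because counting mentions is no substitute for a rule on which text prevails, and the two sentences are themselves operative.

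A reader might infer more than the documents support:

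- **That the design section is uniformly once daily and stands against the rest.** It is not. Its own arm definitions say three times a day, and many sections state no frequency at all.
- **That the pharmacist and the ward nurse would deliver different regimens.** The pharmacist's only stated role is access to the randomisation list. Section 5.4 covers the ratio, blocks and strata and does not mention packs. Prepackaged packs appear in Study Design, without a tablet count.
- **That a patient taking all once-daily doses would be scored at 5/15 = 33% compliance, with consequences for the analysis.** No denominator, adherence threshold or adherence-based population is defined, and the analysis is by intention to treat. No stated analysis would change.
- **That the trial could not say which regimen it tested.** This is conjecture, given observed dosing and pill counts.
- **That the comparison is biased.** The frequency is the same in both arms in each version.
- **That the two once-daily sentences are simply the errors.** The documents do not establish this, and it is not for a statistical review to decide.

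**Conclusion.** The concern holds as an internal contradiction in the statement of the randomised regimen: once daily in two randomisation sentences, three times a day in the arm definitions and every other place that states a frequency. The size is three-fold: 1,100 against 3,300 mg/day and 5 against 15 tablets per course, assuming one 1100 mg tablet per administration.

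The consequence is confined to how the intervention and its exposure are specified, which bears on the reading of both efficacy and safety. The contradiction does not by itself bias the treatment comparison or alter the power statement. Actual misdosing is a risk, not something the documents show would happen. The correction is still necessary, because a dosing rule for the randomised product should not carry two values.

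**What to change.** The sponsor must reconcile the following so that one regimen is stated throughout:

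- the Protocol Summary (Précis, objectives and Description of Intervention);
- the Schematic of Study Design;
- the Objectives;
- Study Design (both the arm definitions and the randomisation sentence);
- section 5.4;
- the dosage and administration text under Study Intervention.

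The number of tablets per administration should be stated explicitly at the same time. The sponsor should then check that pack contents and labels, and the tablet number expected in pill counts, match the reconciled regimen. Which regimen is right is for the sponsor to determine.

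The cost is small: wording changes in whichever sections prove inconsistent, IRB review of the amendment as the protocol requires, and a check of packs and pill-count records. The design, sample size and analysis need no change on this account.
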